## 2. Materials and Methods

### 2.1. Participants

Participant recruitment began in May 2022 and will continue until December 2023. Athletes from the national clubs and teams of different sports in Jordan will be invited to participate in this study. Elite athletes are eligible if they satisfy the following criteria: (1) being 16 years of age and older and (2) have a complaint of sleep impairment determined by a global score >5 on the Pittsburgh Sleep Quality Index (PSQI).

Exclusion criteria for the study will include any of the following: the use of sleep medications or other interventions interfering with sleep and sleepiness, more than one concussion in the past year, using a pacemaker, pregnancy, diagnosis of migraines with a high frequency of episodes, wearing a metal implant, or epilepsy. 

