### 2.3. Randomization Allocation and Blinding

Participants will be allocated consecutively to randomization using the tool from the randomization.com website (http://www.randomization.com, Accessed date: 10 May 2022) by a researcher who is not in contact with any participant. The investigators will use the suggested first generation for RCT studies. The included participants will be randomly allocated to the parallel tDCS or control groups in a balanced allocation ratio of 1:1. Allocation concealment will continue until the end of the study.

All assessment, evaluation, and intervention procedures will be carried out by examiners who will be blinded to the allocation of the participants. A trained research assistant that is not otherwise connected with the study will set the stimulation characteristics as indicated by the information in a sealed envelope opened upon the participants’ visits (real or sham). The mode of stimulation will not be revealed to the participants or investigators.

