### 2.5. Procedures

The research procedure will be explained to eligible athletes if they agree to participate. Informed consent will be obtained from each participant. Figure 1 demonstrates the CONSORT flow diagram for this study. Baseline assessments (T0) will be conducted for demographic, health, and sport-related information, clinical characteristics, and primary and secondary outcome measures at baseline. Post intervention assessments (T1) for comparing the immediate efficacy between the two groups of primary and secondary outcome measures will be performed directly after completion of the intervention protocol. Follow-up assessments (T2) will be conducted 1 month after the end of the intervention.

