### 2.12. Statistical Analysis

The participants’ characteristics and outcome measures at baseline will be compared between the two groups using the Kruskal–Wallis test. Data will be screened for missing data, normality, and outliers. For variables that are not normally distributed, non-parametric tests will be used. The normally distributed data will be analyzed by repeated measures analysis of variance (ANOVA) to evaluate the therapeutic effect and changes between the two groups and within groups (group: sham vs. real tDCS) × (time: pre- vs. post-intervention vs. 1-month follow-up). Post hoc analysis will be applied to determine the exact groups with significant changes if significant findings appear. For the variables not normally distributed, we will use Friedmann’s test. The correlation between the changes in the Actigraph results with the athletes’ characteristics, DAAS-21, SF-12 pain, general health, role (emotional), and mental health domains at baseline will be analyzed by repeated measures linear regressions to understand the mechanism of improvement. The data will be analyzed using SPSS software, and a conservative *p*-value of 0.05 will be considered.

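### For outcomes that fail the normality screen the only test named is Friedman's, which has no group factor, so no comparison of real with sham tDCS is specified for them

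*Protocol article*

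**What the plan says.** The trial is a two-arm parallel comparison: section 2.3 has participants "randomly allocated to the parallel tDCS or control groups in a balanced allocation ratio of 1:1". Section 2.5 gives the purpose of the post-intervention assessment (T1) as "comparing the immediate efficacy between the two groups of primary and secondary outcome measures", with a further assessment (T2) one month after the intervention ends.

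Section 2.12 then sets the analysis by branch:

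- **Normal outcomes:** "The normally distributed data will be analyzed by repeated measures analysis of variance (ANOVA) to evaluate the therapeutic effect and changes between the two groups", with group (sham, real) crossed with time (three visits).
- **Non-normal outcomes, general statement:** "For variables that are not normally distributed, non-parametric tests will be used".
- **Non-normal outcomes, named test:** "For the variables not normally distributed, we will use Friedmann’s test".
- **Baseline only:** Kruskal–Wallis between the two groups.
- **Post hoc rule**, placed between the ANOVA sentence and the Friedman sentence: "Post hoc analysis will be applied to determine the exact groups with significant changes if significant findings appear".

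No rank-based comparison of the arms at T1, at T2 or on change from baseline is named.

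**The concern.** The two branches answer different questions. The ANOVA branch contains the group and group-by-time terms that a parallel trial needs. The Friedman branch has no group term. Run on all participants together, it asks whether scores move over time. Run separately in each arm, it gives two within-arm p-values, and a difference in significance between them is not a test of the difference between arms.

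This may reach the main results. ISI and ESS are bounded questionnaire scores, wake after sleep onset is a duration and sleep efficiency is a ratio. All four are listed as primary (section 2.7), and any of them could fail a normality screen. If one does, the analysis named for it could report improvement over time, or improvement in one arm only, and that could be read as efficacy without real tDCS ever having been tested against sham.

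**Working it through.** **1. Number per arm.** Section 2.4 gives d = 0.7012, two-sided alpha 0.05, 80% power and a minimum of 70.
- A two-sample t-test needs 32.9 per arm, so 33 per arm and 66 in total.
- A two-group Wilcoxon-Mann-Whitney test with a normal parent needs 32.915 × π/3 = 34.47 per arm, so 35 per arm and 70 in total. This matches the stated minimum.
- Adding 20%: 70 × 1.20 = 84, as stated.

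The article does not say which test was used for sizing. The match suggests a between-group rank test but does not prove it. The checks below use 35 per arm.

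**2. Does the arm enter Friedman's statistic?** With n participants, k = 3 visits and R_j the sum over participants of the within-person rank of visit j,

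Q = [12 / (n·k·(k+1))] · Σ R_j² − 3·n·(k+1).

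No arm label appears. As a check, 100 was added to every value in one arm of a simulated data set of 70. Chi-square stayed at 0.8857 and p at 0.642. A constant difference between the arms, however large, is invisible to the test.

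**3. Error rates with no tDCS effect.** Assumptions, none of them from the article: 35 per arm, three visits, the same improvement in both arms at T1 and T2, 3000 trials per setting. With visit correlation 0.5, across repeated runs:

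| Common improvement (SD) | Pooled Friedman significant | Real arm significant, sham not |
|---|---|---|
| 0 | about 5% | about 5% |
| 0.3 | 57–58% | 21–23% |
| 0.4 | 82–84% | 23–25% |
| 0.5 | 96% | 19–22% |
| 0.7 | 100% | 4–5% |

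Mann-Whitney on the T0-to-T1 change rejected in about 5% of trials throughout.

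The last column rises and then falls for a simple reason. The arms are independent, so if each rejects with probability p, the chance that only the real arm is significant is p(1 − p), which cannot exceed 0.25. At 0.5 SD, for example, per-arm rejection rates of 0.735 and 0.706 give 0.735 × (1 − 0.706) = 0.216. Adding the reverse pattern, 0.706 × (1 − 0.735) = 0.187, gives 0.403 discordant in either direction.

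Over correlations 0.3 to 0.7 and improvements 0 to 0.7 SD, the real-only pattern runs from about 0% to 25% and pooled Friedman from about 5% to 100%. At correlation 0.7, the real-only rate is about 8–9% at 0.5 SD and below 1% at 0.7 SD.

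**4. The opposite failure.** With log-normal data and correlation 0.5, let the real arm improve by 0.35 SD and the sham arm worsen by 0.35 SD on the log scale, a true difference of 0.7 SD. Pooled Friedman rejected in 4.1% of trials and Mann-Whitney on change in 72.5%.

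**The case against.** The strongest reply is that the general sentence on non-parametric tests is plural and open, and that section 2.5 states a between-group aim, so the investigators may well intend a between-arm rank test. That stands to this extent: a reader might infer that these outcomes will certainly receive no randomised comparison, and the article does not say so. It supports only that none is specified and that the one test named cannot supply it. The point is not merely a detail left to an analysis plan, because the article itself commits to a particular test.

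Four other stronger readings are tempting and go too far.

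- **Post hoc sentence.** A reader might take it to prescribe within-arm tests. It follows the ANOVA sentence, and contrasts after a group-by-time interaction fit its wording too. It is ambiguous, not shown to be wrong.
- **Size.** A reader might take a false real-only pattern in about one trial in five as the expected rate. That is near the peak of the assumed range, and stronger or weaker common improvement gives much less.
- **Regression to the mean.** Entry requires a PSQI above 5, so some fall in PSQI and related scores is plausible in both arms. Extending this to the actigraphy outcomes is weak, because the Discussion itself cites low correlation between subjective and objective sleep measures.
- **The ANOVA branch.** A reader might conclude that it needs replacing as well. Nothing here shows that, since it contains the right comparison.

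It is also fair that the branch is conditional: if every primary outcome passes the screen, Friedman's test decides none of them.

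**Conclusion.** The point holds in this form: section 2.12 specifies no real-versus-sham comparison for any outcome that fails the normality screen. The defect is structural and depends on no simulation setting, because Friedman's statistic does not use the arm. The simulated ranges show only how misleading a time-only result could be, and they depend on the assumed correlation and common improvement. Which outcomes, primary or otherwise, would enter this branch cannot be known from the article. A single primary outcome there would lack a specified efficacy test, which is reason enough to settle the wording before any data are analysed by arm.

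**What to change.** For the non-normal branch, replace Friedman's test as the efficacy analysis with a named between-arm analysis at T1 and at T2. Suitable choices are a baseline-adjusted rank ANCOVA or, more simply, a Mann-Whitney test on change from baseline. Friedman's test, if kept, should be labelled a descriptive within-arm summary. Reword the post hoc sentence so that it means real-minus-sham contrasts at T1 and T2, and state that differing within-arm significance will not be taken as evidence of efficacy. The ANOVA branch need not change on this account. The cost is a few sentences in section 2.12, with no new data and no additional participants.

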### 2.4. Sample Size Calculation

The sample size was calculated using G*Power software according to the study of Charest et al. (2021) [23]. The study found d = 0.7012 for the Cohen’s effect size of tDCS on PSQI as the screening outcome of this study. Based on a 0.7012 effect size, bidirectional alpha of 0.05, and 80% test power, a minimum of 70 participants are required for this study. The sample will be increased by 20% to compensate for possible dropouts, and an overall sample of 84 participants will be included in this study.

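### The only test named for non-normal outcomes, Friedman's, has no group factor, so as written those outcomes get no post-baseline real-versus-sham test

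*Protocol article*

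**What the plan says.** Section 2.12 splits the efficacy analysis by a normality screen.

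- **Normal outcomes:** "The normally distributed data will be analyzed by repeated measures analysis of variance (ANOVA) to evaluate the therapeutic effect and changes between the two groups". The factors are "group: sham vs. real tDCS) × (time: pre- vs. post-intervention vs. 1-month follow-up", so treatment arm is in the model.
- **Non-normal outcomes:** first a general statement, "For variables that are not normally distributed, non-parametric tests will be used", and later the specific one, "For the variables not normally distributed, we will use Friedmann’s test".
- **Other between-group material:** Kruskal–Wallis appears once, for baseline: "outcome measures at baseline will be compared between the two groups using the Kruskal–Wallis test". A follow-up rule, placed directly after the ANOVA sentence, reads "Post hoc analysis will be applied to determine the exact groups with significant changes if significant findings appear" and names no test.

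The design is a 1:1 parallel, sham-controlled trial (sections 2.3 and 2.11). Section 2.5 says that the T1 assessments are "for comparing the immediate efficacy between the two groups of primary and secondary outcome measures". Section 2.4 states that "a minimum of 70 participants are required for this study", without naming the test behind that number.

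**The concern.** The two branches do not answer the same question. The ANOVA branch asks whether the arms differ over time. The Friedman branch asks whether visits differ within athletes. Moving an outcome from one branch to the other because of its distribution therefore removes the randomised comparison.

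Shared improvement is plausible here. Athletes enter because of a PSQI score above 5, which invites regression to the mean, and the sham is designed to feel like real stimulation. A test of time alone would pick up such improvement, and in a section about therapeutic effect it could be read as efficacy. A true effect of stimulation would have no between-arm estimate or interval. The rule has no exemption for primary outcomes, so actigraphy measures, ISI and ESS could all be affected.

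**Working it through.** **1. The plan's own figure.** Inputs from section 2.4: d = 0.7012, two-sided alpha 0.05, power 80%. Equal arms come from section 2.3.

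- Normal approximation: n = 2(1.960 + 0.842)² / 0.7012² ≈ 31.9, so 32 per arm, total 64.
- Two-sample t-test: 32.9, so 33 per arm, total 66.
- Wilcoxon–Mann–Whitney with normal parent: 32.915 / (3/π) = 34.47, so 35 per arm, total 70.
- Dropout: 70 × 1.2 = 84, as stated.

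The stated 70 is matched exactly by a two-group rank test. Because section 2.4 names no test, this only suggests that a between-arm rank comparison was in mind.

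**2. What Friedman's test uses.** With n athletes, k visits and R_j the sum over athletes of the within-athlete ranks at visit j:

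Q = 12 / [n k (k+1)] × Σ R_j² − 3n(k+1)

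For k = 3 this is Q = Σ R_j² / n − 12n. With 70 athletes it is Σ R_j² / 70 − 840. The arm label does not enter, so exchanging real and sham labels among athletes leaves Q unchanged. Pooled, it tests time. Run once per arm, it gives two within-arm p-values and no test of their difference.

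**3. Illustration with no stimulation effect.** Assumed, not from the documents: lognormal outcome, three visits with correlation 0.5 on the log scale, 35 per arm, and the same improvement in both arms at T1 and T2.

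| Shared shift (SD) | Friedman pooled, rejects | Friedman per arm: real significant, sham not |
|---|---|---|
| 0.1 | about 11% | about 7–8% |
| 0.2 | about 27% | about 12% |
| 0.3 | about 55% | about 22% |
| 0.4 | about 84% | about 25% |
| 0.5 | about 96% | about 20% |
| 0.7 | about 100% | about 5% |

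A between-arm Mann–Whitney test on the T0-to-T1 change stays at about 4–6% throughout. Repeat runs move the Friedman entries by a few points at most.

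The last column can be checked by hand. The arms are independent, so the probability is π_real × (1 − π_sham), where π is the per-arm rejection rate:

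- 0.3 SD: 0.314 × (1 − 0.298) = 0.220
- 0.5 SD: 0.719 × (1 − 0.722) = 0.200
- 0.7 SD: 0.947 × (1 − 0.952) = 0.045

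With equal rates this product cannot exceed 0.25, reached at π = 0.5. With no shift at all it is 0.05 × 0.95 = 0.0475. A valid two-sided 5% test favours real stimulation by chance in 2.5% of trials.

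**4. Pooled Friedman does not separate the two situations.** With a shared shift of 0.5 SD it rejects in 96% of trials without a stimulation effect, and in 100% when an effect of 0.7012 SD is added to the real arm.

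**The case against.** The strongest reply is that the article is a condensed text. It speaks of non-parametric tests in the plural, its post hoc sentence shows an intention to compare groups, and a SAP that is not shown may name a between-arm test. This stands against one stronger reading: a reader might infer that the trial has no real-versus-sham comparison for these outcomes at all. The documents do not support that. They show that none is named after baseline, and that the one test named cannot supply it. The reply does not remove the defect. The plural phrase identifies no test, Kruskal–Wallis is confined to baseline, and the post hoc rule depends on a prior significant result, which after Friedman's test concerns time. This is a specific choice that does not fit the question, not a detail left for later.

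Four further inferences should be resisted.

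- **That any shared change produces a significant result.** At 0.1 and 0.2 SD the pooled test rejects in only about 11% and 27% of trials.
- **That the authors plan to contrast per-arm p-values.** The text does not say whether Friedman's test is pooled or run by arm. The per-arm column describes a possible misuse, and its rate is low at both ends of the range of shifts.
- **That section 2.4 contradicts the choice.** It names no test that could be contradicted. The conflict is with section 2.5.
- **That most outcomes will land in this branch.** No distributions are given and no normality test is named. Simulated screen results depend heavily on assumptions. For a PSQI truncated at above 5 with assumed underlying mean 10 and SD 3, Shapiro–Wilk rejects in 92% of samples at n = 84, but in about 36–38% at n = 42. The PSQI cut applies at eligibility, and PSQI is a secondary outcome.

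**Conclusion.** The point holds in this form: for outcomes judged non-normal, the only test named cannot compare the arms, and no post-baseline between-arm test is named in its place. This is wrong as written and conflicts with the between-group purpose in section 2.5. Outcomes judged normal are not affected, since their ANOVA includes the group factor.

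That Friedman's test has no group factor follows from its formula and needs no assumption. The size of the consequence does rest on assumptions. Under those in the illustration, shared improvement of 0.1 to 0.7 SD gives a significant pooled result in about 11% to 100% of trials with no stimulation effect, against about 5% for a between-arm rank test. The number of outcomes exposed cannot be determined from the document.

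**What to change.** Replace the Friedman sentence with one pre-specified between-arm analysis, valid under non-normality, for T1 and for T2. The estimate and 95% CI should come from the same method as the test. Two suitable options:

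- a Mann–Whitney test comparing the arms on change from T0, reported with the Hodges–Lehmann difference in change and its 95% CI; or
- a baseline-adjusted analysis, such as ANCOVA with robust or bootstrap confidence intervals, giving both the test and the estimate.

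A baseline-adjusted test should not be paired with an estimate from unadjusted change, because the two can disagree. If Friedman's test is kept, limit it to describing change within an arm and state that it supports no efficacy claim.

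The cost is a sentence or two in section 2.12 or the SAP, with no new data, participants or visits. It should be done before unblinding, so that the between-arm test is not chosen with the results in view.

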## 3. Discussion

The planning of sleep interventions for athlete populations is different than for other populations, such as as neurological or psychological populations. It requires special considerations for the following reasons. First, the prevalence of sleep disturbances in athletes is high. Second, sleep medication can negatively influence sports performance by impairing the efficacy of resistance, prolonged endurance, and high-intensity exercises [35]. Finally, the current interventions for sleep require a long time and commitment, making adherence challenging [1]. Therefore, we suggest that using a robust intervention method such as tDCS is more feasible for athletes.

This study will assess the effect of bilateral anodal tDCS stimulation specifically over the right and left DLPFCs through small electrodes. The only tDCS study [23] that was conducted for athletes reported that the stimulation was for frontal areas without specifying the targeted areas. The tDCS programs for sleep were generally for the left DLPFC in other populations [19]. The selected tDCS stimulation protocol (bilateral anodal) to improve sleep quality is novel in athletes.

The bilateral anodal tDCS could improve sleep via direct and indirect effects on sleep structures [16]. The right and left prefrontal cortices have important roles in sleep regulation and showed decreased activity in people with poor sleep quality and insomnia [36]. Bilateral DLPFC anodal stimulation might induce the ‘top-down’ pathway of sleep–wake regulation [37]. DLPFC networks generate slow oscillations that are biphasic changes in the membrane potential from a hyperpolarized state (down phase) to a depolarized phase (top phase) (<1 Hz) [38]. Furthermore, tDCS could increase the NREM2 sleep stage and decrease slow wave sleep stage regulation [18]. In addition to the direct effects, the tDCS could improve pain, depression, or anxiety and therefore sleep [16]. To understand the mechanism of improvement, correlation analysis of the changes in objective sleep results with athletes’ characteristics and secondary outcomes at baseline will be conducted.

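### The planned mechanism analysis uses baseline DASS-21 and SF-12 values, which can show prognosis or effect modification but not that tDCS works through pain, depression or anxiety

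*Protocol article*

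**What the plan says.** The analysis is described twice in the protocol article.

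- Section 2.12 (Statistical Analysis) sets the outcome and the explanatory variables: "The correlation between the changes in the Actigraph results with the athletes’ characteristics, DAAS-21, SF-12 pain, general health, role (emotional), and mental health". The same sentence goes on to give timing, method and purpose: "domains at baseline will be analyzed by repeated measures linear regressions to understand the mechanism of improvement".
- Section 3 (Discussion) repeats the plan as a "correlation analysis of the changes in objective sleep results with athletes’ characteristics and secondary outcomes at baseline will be conducted".

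Just before that, the Discussion gives the indirect route that the analysis is meant to illuminate: "In addition to the direct effects, the tDCS could improve pain, depression, or anxiety and therefore sleep".

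On data collection, section 2.5 (Procedures) covers the primary and secondary outcomes at T0. It says that the T1 assessments of the "primary and secondary outcome measures will be performed directly after completion of the intervention protocol". It then adds: "Follow-up assessments (T2) will be conducted 1 month after the end of the intervention". DASS-21 and SF-12 are secondary outcomes (section 2.8), so their change from T0 to T1 will be available.

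**The concern.** The indirect route is a statement about mediation: treatment changes pain, mood or anxiety, and that change alters sleep. To examine it, one needs what happened to those measures after randomisation. The plan uses only their values before it.

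An association between a baseline score and later change in sleep has other readings. The score may predict change in both arms alike (prognosis), it may reflect regression to the mean in the score, or it may mark athletes who respond differently to real stimulation (effect modification). None of these shows the route by which tDCS acts. At stake is the interpretation of this one analysis: a positive finding could be taken as evidence for a mechanism it does not test, and a null finding as evidence against a mechanism that is at work.

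**Working it through.** **Step 1: timing and purpose.** In section 2.12 taken alone, the baseline qualifier might be thought to attach only to the SF-12 domains. The Discussion removes the doubt, because it applies the qualifier to the secondary outcomes as a whole. Both places give understanding the mechanism as the aim. The method's name, repeated measures regression, does not alter this: the outcome may be repeated, but the stated explanatory values are those at T0.

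**Step 2: what a baseline coefficient contains.** The article gives no figure to reproduce, so a simple model serves. Let G be the arm (1 = real tDCS), M0 and M1 a mediator score before and after treatment (higher = worse, baseline SD 1), and Y the improvement in sleep.

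- M1 = ρ·M0 − a·G + e, where a is the effect of tDCS on the mediator
- Y = −b·(M1 − M0) + u, so the whole treatment effect runs through the mediator

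Substituting the first line into the second:

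Y = b(1 − ρ)·M0 + a·b·G + (u − b·e)

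The mediated effect, a·b, sits entirely in the arm term. The baseline coefficient, b(1 − ρ), does not contain a. With assumed values a = 1.0 and b = 0.7:

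- ρ = 0.6: baseline coefficient 0.7 × 0.4 = 0.28, mediated effect 1.0 × 0.7 = 0.7.
- ρ = 1: baseline coefficient 0.7 × 0 = 0, mediated effect still 0.7.
- ρ = 0.6 and a = 0 (tDCS does nothing to the mediator): baseline coefficient still 0.28, mediated effect 0.

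So the baseline coefficient can be zero under full mediation and non-zero under none. The arm-by-baseline coefficient is zero throughout this model.

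**Step 3: illustration by simulation.** Assumptions: 35 per arm (the article's minimum of 70 in section 2.4), 1500 runs, a = 1.0 and b = 0.7 in the mediated scenarios, SD 0.8 for e and 0.7 for u. In the scenario without mediation, Y = 0.7·G + 0.4·M0 + u and tDCS leaves the mediator alone. The baseline column comes from a regression on arm and baseline. The interaction column adds arm × baseline. The last column requires both arm → change in M and change in M → Y to be significant, adjusted for baseline M.

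| Scenario | Baseline term significant | Arm × baseline significant | Joint test on change in M significant |
|---|---|---|---|
| Full mediation, ρ = 1 | 5.2% | 5.4% | 100% |
| Full mediation, ρ = 0.6 | 71.2% | 6.2% | 99.9% |
| No mediation, baseline prognostic | 99.3% | 4.7% | 0.2% |

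In the first row the baseline term is at about its nominal 5% although mediation is complete. In the third it is nearly always significant although there is no mediation. In the second, the signal comes from regression to the mean in the score, as the algebra shows. The rates depend on the assumed effects and are not predictions for this trial. In particular, the near-certain detection in the last column reflects the large effects assumed.

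**The case against.** The strongest reply is that this is a search for predictors of improvement under an unlucky label. Many of the listed characteristics, such as date of birth or type of sport (section 2.6), could not be mediators, and the Discussion calls the work a correlation analysis. On that reading a change of wording is enough. Much of this stands: relabelling is the main remedy, and mediation is needed only if the indirect route is to be examined. It does not rescue the stated purpose, which both sections give in the same terms.

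Four stronger readings are tempting, but the documents do not support them.

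- *That the regression pools both arms without an interaction.* The article lists no model terms. An article commonly leaves these to the full protocol or analysis plan, so the point about prognosis versus effect modification is conditional.
- *That pain, depression and anxiety are the proposed mechanism.* They are one route, offered in addition to direct effects on sleep regulation.
- *That a definite number of false mechanisms should be expected.* The article fixes neither the number of models nor the handling of T1 and T2. Such a count would also measure multiplicity, whereas this defect would remain with a single test.
- *That every significant coefficient will be reported as a mechanism.* That predicts the report; the article makes no such commitment.

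**Conclusion.** The point holds in limited form. As written, the baseline analysis cannot show that tDCS improves sleep through pain, depression or anxiety. It can show prognosis, or effect modification if an arm-by-baseline term is fitted, and even a clear interaction would not establish the route.

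The conclusion rests on the order of events, which the article itself fixes, and not on the simulated rates. It is not a detail left to another document, since an analysis plan that carried out section 2.12 faithfully would keep the mismatch.

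Its reach is one explanatory analysis. The comparison of real and sham tDCS over time, the sample size and the data collected are unaffected. It should be corrected before the data are analysed.

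**What to change.** 1. In section 2.12 and the Discussion, rename the baseline analysis an exploratory predictor or effect-modifier analysis and remove the mechanism wording from it.
2. Choose a few named baseline variables and test arm-by-baseline interactions for them. Report main effects of baseline as prognostic only.
3. Optionally, if the indirect route is to be examined, add an exploratory mediation analysis by randomised arm: arm → T0-T1 change in DASS-21 and the chosen SF-12 domains → later (T2) actigraphy, adjusted for the baseline of both mediator and outcome. State that it assumes no unmeasured confounding between mediator and sleep outcome, because the mediator is not randomised.

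Cost: items 1 and 2 are wording and a small amount of analysis. Item 3 is modest extra analysis on assessments already scheduled; section 2.5 does not itemise the T2 measures, but the time factor in section 2.12 includes the one-month follow-up. The drawbacks of item 3 are likely low power at this sample size, which keeps it exploratory, and the fact that a T2 outcome captures only an effect that lasts a month after treatment.
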